### Dose modifications

TMZ dose modifications, delays, or discontinuation should be made in response to toxicities according to the institution’s usual practice. Amended doses and reasons for any modifications will be recorded at each cycle. Suggested guidance for modifications is provided in Appendix 5. If TMZ cycles are delayed due to TMZ related toxicities, then nabiximols/placebo can be continued during the delay if deemed appropriate by the treating clinician. Any patient with two prior dose reductions who experiences toxicity that would require a third dose reduction of TMZ or a delay of > 2 weeks will have their TMZ, and nabiximols/placebo discontinued and be withdrawn from the trial.

If a toxicity suspected to be related to nabiximols/placebo occurs, then dosing can be suspended or amended until the event has resolved. Patients, whose dose is adjusted, may restart the titration at an appropriate dose and return to their MTD gradually by increasing the number of sprays by one spray per day (Table 2). If a participant requires > 2 weeks off nabiximols/placebo or reduce their dose to < 3 sprays/day, then the patient should stop nabiximols/placebo permanently. TMZ can be continued, if appropriate, at the discretion of the treating physician as per local standard of care.

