### Screening and consent

Written informed consent will be obtained from all patients. The investigator will provide information to allow the patient to make an informed decision regarding their participation. The patient summary and information sheet are provided in Appendix 3, with an exemplar informed consent form in Appendix 4. If a participant loses mental capacity during the study, their responsible caregiver will be consulted to determine their suitability of remaining on trial. Any data collected up to the point of withdrawal will be kept on record and used in the trial analysis. If the patient loses capacity and the caregiver decides that the patient may continue to participate in the trial, then the caregiver will be asked to provide trial related information (e.g., information on side effects) on behalf of the patient.

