### Interventions

Patients will be randomised to one of the two treatment arms:

Experimental arm: TMZ with nabiximols.Control arm: TMZ with nabiximols-matched placebo.

All patients will receive non-dose dense TMZ given at 4-weekly intervals (± 3 days for unavoidable delays, bank holidays etc.) up to a maximum of six cycles (pending tolerability) or until disease progression, whichever is sooner. It is recommended that initial doses (in the absence of renal or hepatic impairment) will be:

Cycle 1: TMZ 150mg/m^2^, with dose capping as per local standard practice, once daily (OD) for days 1–5, by mouth (PO), on a 28-day cycle for cycle 1.Cycles 2–6: TMZ 200mg/m^2^, with dose capping as per local standard practice, OD for days 1–5, PO, on a 28-day cycle for cycles 2–6.

Patients who were unable to tolerate 200mg/m^2^ during their initial adjuvant treatment, are permitted to start trial treatment on a lower dose of 150 mg/m^2^ with dose capping as per local standard practice.

Nabiximols or placebo is administered in a self-titration regime (Table 2). This should start as a single spray in the evening of day 1 cycle 1 and gradually titrate to reach an individualised dose based on tolerability. A minimum of three sprays per day is recommended, with the maximum daily dose of 12 sprays. Patients will establish their individualised maximum tolerated dose (MTD) within 14 days of their first dose and continue this regime every day for up to six months (six cycles). If this is not achievable the patient should be permitted to continue in the trial, providing that they continue to receive trial medication, but will not be considered evaluable for the trial and will be replaced.

**Table 2 Tab2:** Nabiximols/placebo titration regimen

Day	Number of Sprays		
	Morning Between waking-up and 12pm	Afternoon Between 4pm and bedtime	Total number of sprays per day
1	0	1	1
2	0	1	1
3	0	2	2
4	0	2	2
5	1	2	3
6	1	3	4
7	1	4	5
8	2	4	6
9	2	5	7
10	3	5	8
11	3	6	9
12	4	6	10
13	4	7	11
14	5	7	12

Taken from the nabiximols Summary of Product Characteristics [29]

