This trial uses a non-commercial supply of nabiximols outside its licenced indication, and is a Class B controlled drug under the Misuse of Drugs Act 1971 so is placed in Schedule 2 of the Misuse of Drug Regulations 2001. All trial sites are therefore required to hold an appropriate Home Office licence, or exemption, and to follow Schedule 2 requirements for the storage and dispensing of nabiximols, adding complexity to the pharmacy aspects of this blinded trial.

Patients will be followed up at 4-weekly assessments for a minimum of 52 weeks from the start of trial treatment or until death, whichever is sooner. MRI scanning will be performed at screening, week 10, week 22, week 30, then 3-monthly after commencing trial treatment as per standard practice. A schedule of events is included in Table 3.

**Table 3 Tab3:** ARISTOCRAT trial schedule of events

Activity	Screening Within 21 days of trial entry	Randomisation	Week 0^#^ Cycle 1	Week 4 Cycle 2 ± 3 days	Week 8 Cycle 3 ± 3 days	Week 10 ± 3 days	Week 12 Cycle 4 ± 3 days	Week 16 Cycle 5 ± 3 days	Week 20 Cycle 6 ± 3 days	Week 22 ± 3 days	Week 24 EOT	Follow Up		
												Week 28	Week 30	As per SoC
Informed consent^1^	X													
Confirm eligibility	X													
MRI scan (RANO criteria)^2^	X					X				X			X	X Minimum 3 monthly
Blood tests^3^	X		X	X	X		X	X	X		X			
Concomitant medication^4^	X		X	X	X		X	X	X		X	X		X
Electrocardiogram^5^	X													
Karnofsky Performance Status^6^	X		X	X	X		X	X	X		X	X		X
Medical history^7^	X													
Physical examination^8^	X		X	X	X		X	X	X		X			
Pregnancy test^9^	X		X	X	X		X	X	X		X			
Urine test for cannabinoid use^10^			X		X						X			
Vital signs^11^	X		X	X	X		X	X	X		X			
TMZ + nabiximols/placebo^12^			X	X	X		X	X	X					
Adverse Events^13^	X		X	X	X		X	X	X		X	X		X
Patient diary			X	X	X		X	X	X					
Health-Related Quality of Life^14^			X		X			X			X			
Survival status^14^			X	X	X		X	X	X		X	X		X

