### Statistical analysis plan

#### Sample size

The target sample size is 234 patients based on testing the null hypothesis of no difference between the treatment arms in terms of OS, i.e., a hazard ratio (HR) = 1 and assumes exponential distribution for survival times. Calculations assume a recruitment period of 18 months and follow-up period of 12 months. As a phase II trial, the design uses a relaxed one-sided significance level of 10% (i.e., α = 0.1) and a randomisation ratio of 2:1 in favour of the experimental treatment arm. The expected median survival time on the placebo arm is 12 months, which equates to a hazard rate of 0.058 [6, 24]. Given these design parameters, the trial requires 132 events to have 80% power (i.e., β = 0.2) to detect a difference with a hazard ratio of 0.68, i.e., median survival time of 17.6 months on the experimental treatment arm and hazard rate of 0.039. Given the results from the phase I trial [16], we believe this is a plausible benefit to target. It is estimated that we need to recruit 222 patients during the 18-month recruitment period to observe this number of events; a further 5% to cover potential dropouts has been added to give a target sample size of 234. The trial includes an initial feasibility study that, based on a pragmatic rationale, will incorporate the first 40 patients recruited.

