#### Outcome analyses

Overall survival time will be analysed using the Kaplan-Meier method to estimate and plot the survivor functions for each treatment arm, together with summary statistics of median and 12-month survival rates. In addition, 6-month and where available 24-month survival rates will be reported. The difference between treatment arms will be estimated using a hazard ratio generated from a Cox regression model. All estimates will be reported with one-sided 90% confidence intervals. The null hypothesis of no difference between the treatment arms in terms of overall survival time will be tested using the Cox regression model. The primary analysis will be on all patients who have received at least two cycles of protocol treatment.

Progression-free survival time will be analysed in the same way as OS. Measures of HRQoL will be reported on each treatment arm as means over time with 95% confidence intervals. The incidence of adverse events will be reported in the case report form (CRF) and patient diaries on each arm and compared descriptively.

Final analysis of the completed phase II trial will occur once all participants have been recruited and followed up for at least 12 months from closure of the trial to recruitment.

The treatment effect will be evaluated for subgroups of patients defined by age (≤ 70 vs. > 70 years), performance status (Karnofsky Performance Status 60–79 vs. 80–100), sex (male vs. female), symptomatic vs. asymptomatic at baseline, numbers of sprays per day and re-resection group.

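### Withdrawing patients from the trial for repeated temozolomide toxicity conflicts with survival follow-up to death and could censor the primary outcome informatively

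*Protocol article*

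**What the plan says.** All references are to the protocol article.

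- **Outcome measures:** the primary outcome is time from randomisation to death from any cause. Patients alive at analysis are censored when last seen alive.
- **Dose modifications, first paragraph:** a patient with two earlier temozolomide reductions, whose toxicity would call for a third or for a delay of more than two weeks, "will have their TMZ, and nabiximols/placebo discontinued and be withdrawn from the trial".
- **Dose modifications, second paragraph:** a patient who cannot stay on the spray stops the spray permanently and may continue temozolomide. Leaving the trial is not mentioned.
- **Interventions, titration:** if the individual dose is not established within 14 days, "the patient should be permitted to continue in the trial, providing that they continue to receive trial medication".
- **Interventions, follow-up:** "Patients will be followed up at 4-weekly assessments for a minimum of 52 weeks from the start of trial treatment or until death". Patient recruitment and a footnote to the schedule of events repeat this one-year minimum.
- **Outcome analyses:** the final analysis takes place "once all participants have been recruited and followed up for at least 12 months from closure of the trial to recruitment".
- **Sample size:** 132 deaths are required, from 222 patients (234 with 5% dropout), over 18 months of recruitment and 12 months of follow-up. Patient recruitment and Trial status now give three years of recruitment.

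**The concern.** A survival endpoint needs vital status on every randomised patient, whatever treatment that patient is still taking. Stopping the drugs is a treatment event; leaving the trial ends data collection. The toxicity rule joins the two. The next paragraph of the same section describes a stop of the spray alone, so the wider wording cannot be dismissed as the authors' only way of saying that a drug is stopped.

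If a site follows the rule literally, a patient who could have contributed a death is censored when last seen alive. Patients who cannot tolerate chemotherapy may well have a different prognosis from those who can, so this censoring is plausibly informative. If more patients leave by this route in one arm, the hazard ratio is biased. Blinding does not prevent that, because toxicity can differ between blinded arms.

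The second issue is length of follow-up. A 52-week minimum is shorter than the sample size calculation needs for all but the last recruits, and the article does not state that survival status is collected to the final data cut-off.

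**Working it through.** **1. The passages side by side**

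- The follow-up text has two end points: at least 52 weeks, or death. The toxicity rule adds a third, trial withdrawal, that can come before either. Both cannot be carried out for the same patient.
- Nothing in the article says that survival status is still collected after such a withdrawal. The nearest sentence, in Screening and consent, is about loss of capacity: "Any data collected up to the point of withdrawal will be kept on record and used in the trial analysis".
- The primary analysis covers patients who received at least two cycles. A patient with two earlier dose reductions will usually have had two cycles, so these patients would mostly be in the primary analysis, with shortened follow-up.

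**2. Reproducing the planned number of deaths**

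Inputs (Sample size): one-sided alpha 0.10, power 80%, hazard ratio 0.68, exponential survival, and two patients allocated to nabiximols for each one to placebo. For the control arm the plan states: "The expected median survival time on the placebo arm is 12 months, which equates to a hazard rate of 0.058". Hence:

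- control hazard = ln 2 / 12 = 0.0578 per month
- experimental hazard = 0.68 × 0.0578 = 0.0393 per month

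With uniform recruitment over R months and F further months, the probability of an observed death at hazard h is

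p = 1 − [exp(−hF) − exp(−h(R+F))] / (hR).

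For R = 18 and F = 12, p = 0.689 (control) and 0.553 (experimental). At the weighted average hazard of 0.0454, p = 0.604.

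N = [1.2816 × √(4.5/0.604) + 0.8416 × √(3/0.689 + 1.5/0.553)]² / (ln 0.68)² = 221.2, so 222.

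Expected deaths = 222 × (0.689/3 + 2 × 0.553/3) = 132.8. Dropout: 222/0.95 = 233.7, so 234. The plan's 132, 222 and 234 therefore reproduce, with every patient followed to a common cut-off (up to 18 + 12 = 30 months for the first recruit).

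**3. Deaths and power under different follow-up**

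Power for D deaths = Φ(0.3857 × √(2D/9) − 1.2816). At D = 132 this gives 79.0%, close to the planned 80%.

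For 12 months per patient, p = 0.500 (control) and 1 − 0.5^0.68 = 0.376 (experimental), weighted 0.417.

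| Survival follow-up | N = 222: deaths, power | N = 234: deaths, power |
|---|---|---|
| Common cut-off, 18 + 12 months | 132.8, 79.2% | 139.9, 80.8% |
| Common cut-off, 36 + 12 months | 157.0, 84.0% | 165.5, 85.5% |
| Each patient 12 months only | 92.6, 68.0% | 97.6, 69.7% |
| Each patient 12 months + 28 days | 97.8, 69.7% | 103.1, 71.4% |

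The last row allows for the 28 days permitted between randomisation and start of treatment.

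**4. Effect of withdrawal on the count alone**

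Assumption, not in the documents: a share w of 234 patients is lost at month 4, unrelated to prognosis. Deaths = (1 − w) × E + w × 38.8, where E is the expected number without loss and 38.8 is the number expected by month 4.

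| w | 18-month recruitment | 36-month recruitment |
|---|---|---|
| 5% | 134.9 | 159.1 |
| 10% | 129.8 | 152.8 |
| 20% | 119.7 | 140.1 |

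With three-year recruitment the count stays above 132 throughout. A larger count does not remove bias from informative censoring.

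**The case against.** The strongest case against is that very little of this is a stated defect.

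- **Scope.** A reader might infer that stopping treatment in general means leaving the trial. The text does not say so. Only the repeated temozolomide-toxicity route is written that way. The titration condition covers only patients who miss the 14-day target, and its purpose is to let them stay.
- **Loss of capacity.** A reader might infer that data stop when capacity is lost. Screening and consent does not say that. The caregiver is consulted, the patient may continue, and the caregiver then supplies information. The sentence on data up to withdrawal says what is kept; it does not say that nothing more is collected.
- **Follow-up.** A reader might infer that the trial will fall short of 132 deaths. But 52 weeks is a minimum, the final-analysis rule demands longer follow-up of early recruits, and 24-month survival is to be reported where available. The two statements can both be met.
- **Size of bias.** A reader might want an inflated false-positive rate. Any such figure needs withdrawal rates by arm and the relative hazard of those withdrawn, and the article gives neither. Under no treatment effect, equal withdrawal mechanisms in both arms cause no systematic bias. The Background reports no difference in treatment-emergent adverse events between arms in the phase I trial, though that is weak evidence (21 patients, dose-dense temozolomide).
- **Condensed article.** Levels of withdrawal and later survival checks may be set out in the full protocol.

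The first four points stand and limit the finding. The last does not dispose of it: the toxicity rule is a statement in the text, not an omission, and it conflicts with the follow-up statement in the same article.

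**Conclusion.** The point holds for one rule. As written, patients meeting the repeated temozolomide-toxicity criterion leave a trial whose primary outcome is death, against the promise of follow-up for at least 52 weeks or until death. The consequence is potentially informative censoring of overall survival, with bias if withdrawal differs by arm. Its direction and size cannot be derived from the documents.

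The follow-up length is a matter for clarification, not a contradiction. Under the final-analysis rule and three-year recruitment, the deaths exceed the 132 required. The shortfall to about 93-98 deaths arises only if every patient's follow-up ends at the minimum. The final analysis is set by calendar and does not wait for 132 deaths, so such a shortfall would not correct itself. These figures assume exponential survival, the design hazard ratio and uniform recruitment.

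**What to change.** 1. In Dose modifications, reword the consequence for these patients: they stop trial treatment and remain in survival follow-up, and where possible progression follow-up, unless they withdraw consent for it. The toxicity criterion itself is untouched.
2. In Interventions, align the titration condition, so that continuing to take trial medication is not a condition for remaining in survival follow-up.
3. In Patient recruitment, Interventions and the schedule footnote, add to the 52-week minimum that survival status is collected for every randomised patient until death or the final data cut-off. This brings them into line with Outcome analyses.

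The cost is a protocol wording change, consent wording if needed, and one survival status check per patient at data cut-off. Recruitment opened in February 2023, so an early change limits the survival data that could be lost.

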## Discussion

### Choice of trial design

A phase II rather than phase III trial design has been chosen for the ARISTOCRAT trial, as the preliminary data on potential efficacy is still sparse. In addition, the feasibility of undertaking such a trial in terms of safety, compliance, and achievability of recruitment needs to be evaluated before embarking on a phase III and this will be done within the early stages of this trial. The choice for the design to be a randomised, double-blind, placebo-controlled trial will ensure an unbiased robust evaluation of the treatment and will allow potential recruitment expansion into a phase III trial should the emerging phase II results warrant this development. In this case, the phase II sample size is synergistic with the requirements for the first stage of a two-arm two-stage phase III trial design.

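### A patient who fails spray titration but completes two cycles is out of the trial's evaluable set under Interventions and in the primary survival analysis under Outcome analyses

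*Protocol article*

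**What the plan says.** Three places in the protocol article bear on this.

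- **Interventions.** "Patients will establish their individualised maximum tolerated dose (MTD) within 14 days of their first dose" and then keep to that dose daily for up to six cycles. The next sentence deals with failure: "If this is not achievable the patient should be permitted to continue in the trial, providing that they continue to receive trial medication", but such a patient "will not be considered evaluable for the trial and will be replaced". Three sprays a day is described as a recommended minimum, not a requirement.
- **Outcome analyses.** "The primary analysis will be on all patients who have received at least two cycles of protocol treatment". No exclusion for failed titration is attached.
- **Dose modifications.** After suspected spray toxicity, patients who need more than two weeks off, or who "reduce their dose to < 3 sprays/day, then the patient should stop nabiximols/placebo permanently", come off the spray. For them, "TMZ can be continued, if appropriate, at the discretion of the treating physician as per local standard of care". Nothing is said here about their analysis status.

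The Discussion (Choice of trial design) states that "a randomised, double-blind, placebo-controlled trial will ensure an unbiased robust evaluation of the treatment".

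**The concern.** Both rules are printed as operative sentences, and for one type of patient they give opposite answers. Nothing in the article says which prevails, so this is a conflict in the text and not a detail left to an analysis plan.

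If the Interventions rule prevails, membership of the primary survival set depends on how well the patient tolerated the spray in the first two weeks. That is observed after randomisation and can be affected by the treatment itself, since active spray and placebo need not be equally tolerable. Blinding does not prevent this: the selection can differ between arms even if nobody knows the allocation. If patients who fail titration also have a different prognosis, the arms are no longer comparable. Recruiting a replacement keeps the event count up but does not put the lost patient back. The claim of an unbiased evaluation is then weaker than stated.

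**Working it through.** **1. The plan's own figures reproduce.** Inputs (Sample size): one-sided α 0.10, power 80%, 2:1 allocation, control median 12 months, hazard ratio (HR) 0.68, accrual R = 18 months, follow-up F = 12 months.

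- Hazards: λc = ln 2/12 = 0.0578; λt = 0.68 × 0.0578 = 0.0393.
- Event probability: P(λ) = 1 − [exp(−λF) − exp(−λ(R+F))]/(λR), giving 0.689 (control) and 0.553 (experimental). The 2:1 average is (0.689 + 2 × 0.553)/3 = 0.598.
- The Lachin–Foulkes formula gives N = 219.9 and 219.9 × 0.598 = 131.5 events, against 222 and 132 stated. Also 222 × 0.598 = 132.8 events, and 222/0.95 = 234.

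The design arithmetic is not in dispute.

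**2. The two rules side by side**, for a patient who fails titration, continues on trial medication and completes two cycles:

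| Rule that prevails | In primary survival analysis? |
|---|---|
| Interventions (not evaluable, replaced) | No |
| Outcome analyses (all with two or more cycles) | Yes |

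The second row assumes that the spray dose such a patient takes counts as protocol treatment, a term the article does not define.

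**3. Power is not the main issue.** With Schoenfeld's formula, 132 events give 79.0% power at HR 0.68. Losing an assumed 5% of events (132 × 0.95 = 125.4) without replacement gives 77.5%. Replacement recovers that loss but not the selection.

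**4. Illustrative size of the selection.** The article gives no titration-failure rate, no prognosis for such patients and no difference between arms, so f and k below are assumptions. Set-up: 148 v 74 patients (222 split 2:1), uniform accrual over 18 months, 12 months' follow-up, median 12 months in both arms (true HR 1), log-rank test at one-sided 10%, 20,000 trials per cell, Monte Carlo error about 0.2 points. A fraction f of each arm has hazard k times the others, and these patients are removed from nabiximols only.

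| k | f | As randomised | After removal |
|---|---|---|---|
| 2 | 1% (about 1.5 of 148) | 10.3% | 11.0% |
| 2 | 2% (about 3) | 10.4% | 11.8% |
| 2 | 5% (about 7) | 10.4% | 14.0% |
| 2 | 10% (about 15) | 10.3% | 18.7% |
| 1.5 | 5% | 9.9% | 12.1% |
| 1 | any | no change | no change |
| 0.67 | 1% | 10.2% | 9.8% |
| 0.67 | 2% | 10.5% | 9.6% |
| 0.67 | 5% | 10.3% | 8.4% |
| 0.67 | 10% | 10.3% | 6.8% |

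At k = 2 and f = 5% the average estimated HR moves from 1.00 to 0.97. If placebo patients are removed at half the rate, the same cell gives 12.5%. As a check on the set-up, power at HR 0.68 as randomised was 79–81%, against 80% stated.

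**5. Allowing for the two-cycle rule.** The table above ignores that rule, which already removes the earliest deaths in both arms. A separate set of runs (8,000 trials per cell, error about 0.3 points) also required survival to day 56. At k = 2 and f = 2%, 5% and 10%, the rates were 11.2%, 13.5% and 17.1%, against 11.8%, 14.4% and 19.2% without the requirement. The direction is the same and the size somewhat smaller.

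**The case against.** The best defence is that the rules are layered: the two-cycle minimum is one filter and evaluability another, as when Treatment compliance says patients with a positive urine test may be unevaluable at analysis. How the filters combine would then be for the analysis plan. This is arguable, but the primary-analysis sentence speaks of all patients with two cycles and names no second filter. Layering also settles the conflict in the worse direction, since it removes patients on tolerability.

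A second objection is that the size rests wholly on assumptions. This stands. With no rate in the article, results run from 6.8% to 18.7%, and nothing changes at equal hazard. The trigger is also loosely worded: a patient who settles at two sprays by day 14 has arguably established a maximum tolerated dose, so the group affected may be small.

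A reader might go further and infer that Interventions and Dose modifications contradict each other for a patient whom toxicity holds below three sprays during days 5–14, when Table 2 has reached three or more. The text does not support that firmly. Dose modifications speaks of reducing a dose and of returning to the maximum tolerated dose, which fits the period after titration. Interventions only recommends three sprays and permits continuation only while trial medication is still taken. Which rule governs is a minor clinical clarification, and it changes no conclusion once the analysis set is fixed.

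**Conclusion.** The point holds as a conflict between Interventions and Outcome analyses over who is in the primary survival analysis. Following the Interventions rule would remove randomised patients on post-randomisation spray tolerability, and replacement does not cure that.

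The size is unknown. Under assumed removal of 1–5% of nabiximols patients only, at twice the hazard of the rest, the one-sided false-positive rate is roughly 11–14% against a nominal 10%, and somewhat less with the two-cycle rule modelled. It falls below 10% if those removed have the better prognosis. If failure is rare, the effect is small.

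It would be wrong to infer that the trial's error rate is inflated by any stated amount, or that the bias must favour nabiximols: the article supplies neither a rate nor a direction. This is a point to consider, worth settling before unblinded efficacy data accumulate at the six-monthly data monitoring reviews, because a later choice of analysis set could look data-driven.

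**What to change.** 1. In Interventions, replace the clause "will not be considered evaluable for the trial and will be replaced" with: *will not be evaluable for spray compliance; any replacement is an additional patient, and the original stays in the overall survival analysis in the randomised arm.*
2. In Outcome analyses, add: *Failure to establish a maximum tolerated dose, or stopping the spray, is not a ground for exclusion from the primary overall survival analysis.*
3. Apply one inclusion rule to every patient in both arms, preferably all patients as randomised. Do not waive the two-cycle requirement for spray failures alone. That would count early deaths among spray failures while excluding other early deaths. In the 8,000-trial runs (failures on nabiximols only, twice the hazard) it gave false-positive rates of 10.1%, 9.6% and 7.9% at 2%, 5% and 10% failure: negligible when failure is rare, but a new bias against nabiximols at 10%.
4. Confirm that survival follow-up continues after the spray is stopped. The article says "Patients will be followed up at 4-weekly assessments for a minimum of 52 weeks from the start of trial treatment or until death", but Interventions ties remaining in the trial to still receiving trial medication, so this is not clearly assured for those who stop.

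The cost is wording in two sections, a note to sites and the follow-up confirmation. The downside is slight dilution of the effect from patients with little spray exposure.
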